### Victim compensation plans

In the event of direct harm related to this study, participants will receive the appropriate medical treatment as determined by a subinvestigator and will be compensated according to the terms of the trial insurance, which will be designated beforehand.

### Dissemination

The results of this trial will be registered on clinicaltrials.gov and CRIS, and will be published in an academic journal. After the publication of this article, important changes to the study protocol and any other changes will be updated regularly on the trial registration site.

## Discussion

Although HPP is used for various musculoskeletal disorders in South Korea, including TMD, there is currently a lack of evidence regarding its efficacy for TMD. In this study, we will conduct an RCT to assess the effectiveness, safety, and economics of HPP in chronic TMD patients compared with PT.

Pharmaco-acupuncture is a form of treatment used in complementary and alternative medicine that combines acupuncture with herbal medicine. By injecting purified herbal medicine extracts into acupoints it provides a combination of the chemical effect from herbal medicine and the physical stimulation effect of needling. Because the herbal extracts are absorbed directly into the treatment site without passing through the digestive system, the effects can be observed immediately; the treatment can be given to patients who cannot receive oral administration and the dose can be easily adjusted [17]. In South Korea, the procedure is performed by doctors of Korean medicine, who are experts in acupuncture and herbal medicine prescriptions.

In this study, we will use HPP as the pharmacopuncture formulation. Hominis placenta (HP), a human placental extract, is the main component of HPP, and has been used in traditional Korean medicine to treat chronic diseases, including frailty, cough, anorexia, and fatigue, by enhancing the body’s resistance. HP is known to be effective for liver regeneration, regulation of the endocrine system [43], antioxidation, nerve regeneration [44], immune enhancement, regulation of menopausal syndrome [45] and wound healing [46]. According to a systematic review [47], HPP has been demonstrated to have anti-inflammatory and antioxidative effects in in vitro and in vivo studies, while clinical trials have reported that HPP is effective for musculoskeletal and neurological conditions, such as alleviating pain, measured by VAS, in chronic ankle sprain patients [48], improving restricted shoulder motion in patients with complex regional pain syndrome [49], and ameliorating peripheral facial nerve palsy [50]. Although HPP is also used in TMD, most studies are case reports. Concomitant treatments make it impossible to identify the effects of HPP alone, although there have been few reports of adverse effects. Therefore, there is a need to collect evidence for HPP through well-designed RCTs.

The advantages of this study are as follows. First, the patient group selection process is clear. In previous studies [51–53], the TMD diagnostic criteria were ambiguous, or there was no distinction between acute and chronic disease, which made it difficult to ensure homogeneity of the patient group. Our study uses a validated Korean version of the RDC/TMD diagnostic criteria, which are standardised and the most widely used criteria [26] and we will only enrol chronic patients, in order to form a precisely defined patient group. Second, the selection of intervention for the treatment group is appropriate. We decided to treat chronic TMD using HP, which is known to aid recovery of injured tissue because it contains growth factor, which promotes wound healing [54]. Moreover, pharmacopuncture is the method of injecting herbal medicine extracts into acupoints; because herbal medicines contain a combination of several ingredients, it is difficult to precisely test the efficacy and safety of individual ingredients, and it is difficult to standardise injected formulations. In anticipation of this debate, we chose HPP, which uses a single active ingredient, is stable, and can be considered relatively safe, since the same extract is already used as an injectant (Laennec®) [50]. Third, the selection of intervention for the control group is objective. According to guidelines for TMD treatment [7], over 90% of TMD can be controlled by conservative treatment, such as PT or drug therapy, but evidence of the effects of several types of conservative treatment is unclear. In a Cochrane review of drug therapy for TMD, [55] it was reported that, even though drug therapy, NSAIDs, benzodiazepines, antispasmodics, and muscle relaxants can be used, there is a lack of clear evidence for their effectiveness. Therefore, considering the statistical data reflecting the clinical reality in guidelines [56, 57], we selected PT (TENS) for the control group.

Nevertheless, our study also has some limitations. First, the study design makes it impossible to blind participants and physicians. However, the physicians and assessors were separated; the assessors did not participate in treatment procedures, performed assessments in a separate space, and were thoroughly blinded to group allocation. Second, psychiatric and psychological factors are known to be important predictive factors for therapeutic effect in TMD [58], but we will not match these factors in the screening stage. This is to minimise selection bias, and, to minimise the effects of these psychiatric and psychological factors, group allocation will be randomised, and we will perform subgroup analysis by K-BDI score to investigate the effects of these factors. Third, because this study includes long-term follow-up, it could be difficult to maintain compliance during follow-up. Accordingly, we will make efforts to improve compliance, such as regular phone calls to participants.

We hope the data from this study will contribute to evidentiary data for standard Korean medicine clinical treatment guidelines. In addition, the study design and methodology can be used as a reference for future clinical trials of acute and subacute TMD or other musculoskeletal disease, as well as studies of other types of pharmacopuncture.

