### Sample size

This is an investigator-initiated clinical trial, and we have calculated the required sample size with reference to similar studies and our clinical experience. First, we set a significance level of α = 0.05 (two-tailed tests), a type 2 error (β) of 0.2, and a test power of 80%. Because there are no previous studies comparing pharmacopuncture with PT for the TMJ, we selected a moderate-to-high effect size for the comparison of mean VAS between the two groups based on our clinical experience, and used Cohen’s d = 0.65 [36]. Using these parameters, we calculated the sample size using G*Power 3.1.7. Based on an effect size = 0.65, the required sample size was estimated to be 39 persons/group (total 78 persons). However, as we plan to use an analysis of covariance (ANCOVA) correcting for the outcome at baseline for our main analysis, we calculated the sample size assuming the correlation between baseline and primary endpoint to be 0.4 [(1–0.4*0.4)*78], and found that the minimum required number of participants was a total of 65 persons [37]. Thus, to account for a dropout rate of 20%, we calculated that the number of participants we need to recruit is a total of 82 persons (41 persons/group).

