### Statistical analysis

As an RCT of chronic TMD patients, this study will compare the difference within and between groups for data on efficacy, safety, and economics. The main analysis will be the ITT analysis, and a PP analysis will also be performed. The demographic results, such as sex, age, occupation, and disease history, and the treatment expectancy will be assessed by group; continuous variables will be presented as the mean ± standard deviation (SD) and categorical variables will be presented as n (%). Differences will be tested using chi-square tests and independent *t* tests. Efficacy outcomes are the changes in continuous outcomes (VAS, NRS, K-BDI, JFLS, EQ5D-5 L, SF-12) at each time point relative to baseline. The primary outcome is the change in VAS from baseline to the primary end point (week 6) in each group. For safety outcomes, we will compare the incidence of AEs between groups; after graphing all the reported ARs in participants who have received treatment at least once, we will calculate the proportion of patients who have experienced AEs in each group, and compare these using chi-square tests and Fisher’s exact test. To compare the HPP and usual care groups, for continuous variables, we will perform an ANCOVA adjusted for the baseline outcome. For categorical variables, we will use chi-square tests of Fisher’s exact test, and to analyse within-group differences between time points, we will use paired *t* tests. Additionally, we will perform an ANCOVA adjusted for baseline outcomes and covariant factors that show a statistically significant difference between the treatment groups at baseline, and we will perform a repeated measures analysis of variance (RM ANOVA) to test differences in the changes across each visit. We will perform subgroup analyses according to RDC/TMD diagnosis (Group Ia, Ib), mouth opening, and K-BDI score. Missing values will be handled in a blinded state, mainly using multiple imputation (MI), last observation carried forward (LOCF) will additionally be used, and sensitivity analyses will be performed. All statistical analysis will be performed using SAS version 9.4 statistical package (SAS Institute, Cary, NC, USA), and statistical significance will be defined as *p* < 0.05.

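### The main week-6 VAS ANCOVA leaves out baseline K-BDI-II, although the protocol calls psychological factors important predictors; prespecifying it as a covariate is a small, almost free gain in precision

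*Protocol article*

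**What the plan says.** The limitations paragraph of the Discussion states that "psychiatric and psychological factors are known to be important predictive factors for therapeutic effect in TMD" and that these factors will not be matched at screening. It then says: "to minimise the effects of these psychiatric and psychological factors, group allocation will be randomised, and we will perform subgroup analysis by K-BDI score". The sentence does not end there. It goes on to say that the subgroup analysis is meant to investigate the effects of these factors.

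The Statistical analysis section fixes the between-group model: "for continuous variables, we will perform an ANCOVA adjusted for the baseline outcome". For the primary outcome the only covariate is therefore baseline VAS. An additional ANCOVA adds factors that differ significantly between the arms at baseline. Subgroup analyses are planned by RDC/TMD diagnosis, mouth opening and K-BDI score. Missing values are handled mainly by multiple imputation.

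The Randomisation section describes 1:1 block allocation and mentions no stratification by K-BDI. Table 1 schedules K-BDI-II in the Week 1 column and at weeks 6, 13 and 25.

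**The concern.** The protocol names a class of factors as important, measures one of them, and then has no prespecified place for it in the main analysis. The two routes it does offer do different jobs.

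- **The subgroup analysis** asks whether the treatment effect differs by K-BDI score. It removes neither K-BDI-related variation nor a chance imbalance in K-BDI from the overall week-6 comparison.
- **The additional ANCOVA** admits K-BDI-II only after a significant baseline test. In a randomised trial that test picks up chance differences. A covariate earns its place by how strongly it predicts the outcome, and a strongly prognostic covariate with a moderate, non-significant imbalance would stay out.

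At stake are some precision that the trial could have from data it already collects, and some protection of the primary estimate against chance imbalance. A covariate fixed in advance also removes a data-driven choice, which has some value here because the Blinding section says that the data analyst is not blinded.

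**Working it through.** **Inputs from the Sample size section.** "we set a significance level of α = 0.05 (two-tailed tests"); "a type 2 error (β) of 0.2, and a test power of 80"%; "used Cohen’s d = 0.65"; "the required sample size was estimated to be 39 persons/group (total 78 persons"); ANCOVA "assuming the correlation between baseline and primary endpoint to be 0.4"; 20% dropout; 82 in total, 41 per arm.

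**Assumed input, not in the documents.** The share R² of residual week-6 VAS variance (after baseline VAS) that K-BDI-II explains. I take 5–10%, a partial correlation of about 0.22–0.32, and show a wider range below.

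**1. The plan's own figure.**
- Two-sample t test, noncentral t, d = 0.65: power is 79.9% at 38 per arm and 80.9% at 39. So 39 per arm, 78 in total, reproduces.
- ANCOVA reduction: (1 − 0.4²) × 78 = 65.52, stated as 65.
- Dropout: 65 / 0.8 = 81.25, so 82. Rounding 65.52 up to 66 would give 82.5, so 83. The stated 82 reproduces to within one patient.

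**2. Power with baseline VAS only.** Residual SD = √(1 − 0.16) = 0.917, so the standardised effect is 0.65 / 0.917 = 0.709. Power is 81.0% at 33 per arm and 88.7% if all 82 are analysed.

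**3. Power with K-BDI-II added.** Residual variance is multiplied by (1 − R²), and one degree of freedom is lost.

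| Assumed R² | Fall in SE, 1 − √(1 − R²) | Power at 33 per arm | Equivalent extra patients, 1/(1 − R²) − 1 |
|---|---|---|---|
| 0 (as planned) | – | 81.0% | – |
| 0.01 | 0.5% | 81.3% | 1% |
| 0.05 | 2.5% | 82.9% | 5% |
| 0.10 | 5.1% | 84.8% | 11% |

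**4. Chance imbalance.** At 41 per arm the standardised difference in mean K-BDI-II has SD √(2/41) = 0.221. Imbalances up to about 1.96 × 0.221 = 0.43 SD do not reach p < 0.05 and so never trigger the additional ANCOVA. With an assumed slope of 0.2–0.3 outcome SDs per K-BDI SD:
- an imbalance at that threshold moves the estimate by 0.43 × 0.2 to 0.43 × 0.3 = 0.09–0.13 SD, or 13–20% of d = 0.65;
- a typical imbalance of one SD (0.221) moves it by 0.04–0.07 SD, or 7–10%.

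**5. What the K-BDI subgroup can show.** If the analysed 65 split evenly by K-BDI, power within one half for d = 0.65 is about 50%. For an interaction of 0.65 SD, the SE is 0.917 × √(4/16.25) = 0.455, so power is about 30%. With all 82 analysed it is about 36%. The subgroup analysis is exploratory.

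**The case against.** The strongest reply is that nothing in the main analysis is wrong. ANCOVA on the baseline outcome is standard, prespecified, matched to the sample-size basis and unbiased under randomisation. Chance imbalance is already reflected in the standard error. The gain is small and rests on a correlation that the documents do not give. The threshold imbalance in step 4 is uncommon, and anything larger would bring K-BDI-II into the additional ANCOVA. All of this stands. It limits the point to a modest improvement but gives no reason to forgo it. The additional ANCOVA would in any case leave the main estimate unchanged.

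Some stronger readings are tempting, and the documents do not support them:

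- **That the protocol relies on subgrouping to minimise psychological effects.** Read whole, the sentence attaches minimising most clearly to randomised allocation and gives the subgroup analysis its own investigative purpose. The opening phrase could be stretched over both clauses, so the wording is at most ambiguous.
- **That K-BDI-II is named as a prognostic factor.** The text speaks of psychiatric and psychological factors in general, as predictive of therapeutic effect. That may mean effect modification, for which a subgroup or interaction analysis is a reasonable tool. It still does not adjust the overall comparison.
- **That the high-K-BDI subgroup will be thin because psychiatric drugs and psychogenic disease are exclusions.** No cut-off or distribution is given, so this is speculation. A narrowed K-BDI range would also tend to shrink the gain from adjustment.
- **That K-BDI-II is first taken after allocation.** Table 1 lists Visit 2 under both Week 0 and Week 1, K-BDI is analysed as change from baseline, and the expectancy item in the same column is explicitly pre-treatment. The timing needs confirming, but it is not shown to be wrong.

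**Conclusion.** The point holds as a minor one, a free improvement. The protocol treats psychological factors as important and collects K-BDI-II, yet it gives that score no prespecified place in the main week-6 ANCOVA. The only route in depends on a significant baseline test, which under randomisation K-BDI-II would pass about 5% of the time. The subgroup analysis serves another purpose and has low power.

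There is no bias, and the sample size of 82 is unaffected. The loss is about 2–4 percentage points of power at 33 per arm if K-BDI-II explains 5–10% of residual VAS variance, and almost nothing if it explains 1%. These gains rest on the protocol's d = 0.65 and correlation of 0.4, and on an R² that must be assumed.

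**What to change.** - In the Statistical analysis section, prespecify the baseline (pre-treatment) K-BDI-II total as a continuous covariate alongside baseline VAS in the week-6 ANCOVA, regardless of any baseline significance test.
- Include the same variable in the multiple-imputation model.
- Keep the K-BDI subgroup as an exploratory K-BDI-by-arm interaction, reported as an estimate with its confidence interval.
- Confirm that the first K-BDI-II in Table 1 (Week 1 column, which includes Visit 2) is completed before treatment. Enrolment began on 17 October 2019, so check this for participants already enrolled as well.
- Optionally, reword the Discussion sentence so that randomisation is plainly the measure against imbalance, covariate adjustment handles the overall comparison, and the subgroup analysis explores effect modification.

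The cost is one degree of freedom and a short amendment, which should be settled before outcomes are seen by arm. It needs no extra patients and, provided the first K-BDI-II is confirmed as pre-treatment, no extra assessments.

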### Trial status

The current protocol is version 2.3 (2 February 2020). First participant was enrolled on 17 October, 2019. We anticipate that the recruitment will be completed by October 2020.

## Data Availability

The datasets analysed during the current study are available from the corresponding author on reasonable request.

## Abbreviations

AAOP: American Academy of Orofacial Pain
AE: Adverse event
ANCOVA: Analysis of covariance
CRF: Case report form
CRP: C-reactive protein
EQ-5D-5 L: EuroQol-5 dimensions 5 levels
EQ-VAS: EuroQol Visual Analogue Scale
hCG: Human chorionic gonadotropin
HIRA: Health Insurance Review and Assessment Service
HP: Hominis placenta
HPP: Hominis placental pharmacopuncture
ICER: Incremental cost-effectiveness ratio
ICF: Informed consent form
iCReaT: Internet-based clinical research and trial
IRB: Institutional review board
ITT: Intention-to-treat
JFLS: Jaw Functional Limitation Scale
K-BDI: Korean version of Beck’s Depression Index
KHIDI: Korea Health Industry Development Institute
LOCF: Last observation carried forward
MI: Multiple imputation
NRS: Numeric Rating Scale
NSAIDs: Non-steroidal anti-inflammatory drugs
PA: Pharmaco-acupuncture
PGIC: Patient global impression of change
PP: Per protocol
PT: Physical therapy
QALY: Quality-adjusted life year
RCT: Randomised control trial
RDC/TMD: Research diagnostic criteria for temporomandibular disorders
RM ANOVA: Repeated measures analysis of variance
ROC: Receiver operating characteristic
ROM: Range of motion
SD: Standard deviation
SF-12: 12-Item Short-Form Health Survey
SOP: Standard operating procedure
SSRI: Selective serotonin reuptake inhibitor
TENS: Transcutaneous electrical nerve stimulation
TMD: Temporomandibular disorder
TMJ: Temporomandibular joint
VAS: Visual Analogue Scale
WHO-UMC: World Health Organization-Uppsala Monitoring Centre
